# Efficacy of a midwife-coordinated, individualized, and specialized maternity care intervention (ChroPreg) in addition to standard care in pregnant women with chronic disease: protocol for a parallel randomized controlled trial

**DOI:** 10.1186/s13063-019-3405-5

**Published:** 2019-05-28

**Keywords:** Pregnancy, Chronic disease, Midwifery, Maternity care, Antenatal care, Psychological well-being, Complex intervention

## Abstract

**Background and objectives:**

The number of women of childbearing age with chronic diseases is rising. Evidence has shown that obstetric complications and poor psychological well-being are more prevalent among this group, in addition to these women reporting experiences of less than satisfactory care. More research is needed to investigate how to best meet the special needs of this group during pregnancy and postpartum. Previous research has shown that care coordination, continuity of care, woman-centered care, and specialized maternity care interventions delivered to women with high-risk pregnancies can improve patient-reported outcomes and pregnancy outcomes and be cost-effective. However, no previous trials have examined the efficacy and cost-effectiveness of such interventions among pregnant women with chronic diseases. This paper describes the protocol of a randomized controlled trial (RCT) of a midwife-coordinated, individualized and specialized maternity care intervention (ChroPreg) as an add-on to standard care for pregnant women with chronic diseases.

**Methods/design:**

This two-arm parallel group RCT will be conducted from October 2018 through June 2020 at the Department of Obstetrics, Copenhagen University Hospital, Rigshospitalet, Denmark. Pregnant women with chronic diseases are invited to participate; women will be randomized and allocated 1:1 to the ChroPreg intervention plus standard care or standard care alone. The ChroPreg intervention consists of three main components: (1) coordinated and individualized care, (2) additional ante- and postpartum consultations, and (3) specialized midwives. The primary outcome is length of hospital stay during pregnancy and in the postpartum period, and secondary outcomes are psychological well-being (five-item World Health Organization Well-Being Index, Edinburgh Postnatal Depression Scale, Cambridge Worry Scale), health-related quality of life (12-Item Short Form Health Survey), patient satisfaction (Pregnancy and Childbirth Questionnaire), number of antenatal contacts, and pregnancy and delivery outcomes. Data are collected via patient-administered questionnaires and medical records.

**Discussion:**

This trial is anticipated to contribute to the field of knowledge on which planning of improved antenatal, intra-, and postpartum care for women with chronic disease is founded.

**Trial registration:**

ClinicalTrials.gov, NCT03511508. Registered April 27, 2018.

**Electronic supplementary material:**

The online version of this article (10.1186/s13063-019-3405-5) contains supplementary material, which is available to authorized users.

## Background

In Denmark and worldwide, the number of individuals living with chronic disease is rising [1, 2], and more than one in three Danish adults live with one or more chronic diseases [1]. The management and prevention of chronic disease is a worldwide major public health problem and one of the issues most targeted by the World Health Organization (WHO) [2].

The number of pregnant women affected by chronic diseases such as autoimmune disease, cardiovascular disease, and endocrine disease is also rising, in 2015, the prevalence in Denmark was 16% among pregnant women [3], and international studies report a prevalence between 16% and 27% [4, 5]. The observed rise in chronic disease among pregnant women reflects the rise in chronic disease in the general population [1]. Factors also contributing to this rise include the increasing age of childbearing women, improvements in medical and surgical treatment options, increased use of assistive reproductive technologies, and improvements in diagnostic challenges with better registration of correct diagnoses [3, 6].

Pregnant women with chronic diseases are a vulnerable group. Overall, these women have a higher risk of preterm birth, pregnancy complications such as gestational diabetes and preeclampsia, operative deliveries, postpartum depression, and longer hospitalization during pregnancy and postpartum [5–9]. In addition to this, children of women with chronic diseases have a higher risk of low birth weight, low Apgar score, and birth defects [10–12]. For some women, their chronic disease may be worsened by pregnancy [13], whereas in other cases of disease, women may experience remission from symptoms during pregnancy [10, 14]. Furthermore, in diseases such as sclerosis and rheumatoid arthritis, there is an increased risk of postpartum flares [14–16].

In qualitative studies, women with chronic diseases indicate that information given by caregivers can be uncoordinated and divergent (e.g., information about medication safety, mode of delivery, and breastfeeding). Women also described less than satisfactory care from midwives and doctors in relation to discussing how to distinguish symptoms of pregnancy and what relates to the disease and to prepare women for what to expect during pregnancy [16]. In addition to these experiences, women described a general experience of “feeling abandoned” postpartum and how support for and understanding of their needs were lacking at the time of discharge [17, 18].

The consequences of the increasing population of pregnant women with chronic diseases are numerous, including a higher demand on maternity care providers to skillfully manage pregnancies complicated by chronic diseases. Furthermore, this increase calls for all maternity care providers to provide coordinated care and consistent counseling [19–21] and to support the pregnant woman in her ability to manage her everyday life with a chronic disease both during pregnancy and postnatally as a new mother [18]. It is therefore important that care providers apply highly specialized medical knowledge combined with an ability to provide psychosocial support in the care of this vulnerable group of pregnant women [6, 16, 22].

Previous randomized controlled trial (RCTs) that evaluated the effect of maternity care interventions for women with high-risk pregnancies have found that the following components had a positive effect on patient-reported outcomes such as patient satisfaction and health economic outcomes such as cost reduction and reduction in length of hospital stay (LOS): implementation of specialized multidisciplinary teams [20, 21, 23], care coordination [19, 24], continuity of care [25], antenatal and postpartum telephone-based support [26], and maternity care with focus on care transitions [22]. In a review of RCTs [22], the introduction of nurse specialist care during pregnancy and the postpartum period of pregnant women with epilepsy demonstrated a positive effect on satisfaction of care provided and a reduction in LOS. To our knowledge, no previous RCT has evaluated the effect of the implementation of a midwife-coordinated, individualized, and specialized maternity care intervention as an add-on intervention to standard care delivered to pregnant women with chronic diseases.

### Aim

The aim of this RCT, the ChroPreg Trial, is to evaluate the efficacy of a midwife-coordinated, individualized, and specialized maternity care intervention as an add-on to standard care for pregnant women with chronic diseases. The primary outcome is LOS measured in days of hospitalization from study inclusion until 2 weeks after delivery. Secondary outcomes are patient-reported psychological well-being, health-related quality of life, satisfaction with care, antenatal contacts, and pregnancy and delivery outcomes.

### Hypothesis

The trial was designed to evaluate the effect of a midwife-coordinated, individualized, and specialized maternity care intervention provided to pregnant women with chronic diseases. We hypothesize that this complex intervention with all its components will have a positive impact on the self-reported psychological well-being of the participants, increase health-related quality of life and satisfaction with the care provided, and enhance the participants’ ability to cope with everyday life during pregnancy and in the immediate postpartum period. We hypothesize that the sum of these components will reduce the total number of days of hospitalization.

Previous trials with complex maternity care interventions with nurse specialists and midwifery continuity-of-care models have shown a reduction in LOS. Tracy et al. [25] showed a mean reduction in LOS of 0.38 days (95% confidence interval, 0.18–0.56) in the postnatal hospital stay among a population of mixed-risk pregnant women (*n* = 1748). We expect that the reduction in LOS will be greater in this trial with a population of high-risk pregnant women with chronic disease. In addition, we will measure LOS both antenatally and postpartum from the time of inclusion and up until 2 weeks after delivery.

## Methods/design

### Study design

The ChroPreg trial is a two-arm parallel-group investigator-initiated RCT. Participants will be randomized to either a midwife-coordinated, individualized, and specialized maternity care intervention (ChroPreg) as an add-on intervention to standard care or standard care alone with a 1:1 allocation. The trial is designed in accordance with the Consolidated Standards of Reporting Trials (CONSORT) guidelines for RCTs [27], extended in the better reporting of interventions: Template for Intervention Description and Replication (TIDieR) checklist and guide [28] (Additional file 1), and in accordance with the Standard Protocol Items: Recommendations for Interventional Trials (SPIRIT) guidelines for reporting trial protocols [29] (Additional file 2).

### Study setting

The study will take place at the Department of Obstetrics, Copenhagen University Hospital, Rigshospitalet, Copenhagen, Denmark. The department is highly specialized and in addition to serving as a birth facility for women living in the local area of the hospital in Copenhagen, it is a tertiary referral center for a large geographical area. In 2017, 5471 women gave birth at the hospital, and 700 of these women had one or more chronic diseases. Participants will be recruited from among the women attending antenatal care at Rigshospitalet. In Denmark, all women with normal pregnancies receive antenatal care primarily from midwives, whereas pregnant women with chronic disease and complicated pregnancies receive obstetrician-led antenatal care, including consultations with midwives.

### Inclusion and exclusion criteria

The Danish Health Authorities define chronic disease as a prolonged disease or a disease that continually recurs [30]. Eligible participants will be pregnant women with one or more chronic diseases diagnosed before pregnancy and for which the pregnant woman is followed by an obstetrician during pregnancy, aged ≥ 18 years, able to understand spoken and written Danish, give informed consent, pregnant with a single live fetus, and be between weeks 12 and 19 of pregnancy at the time of inclusion. Potential participants will be excluded from the study for the following reasons: multiple pregnancy, substance abuse, psychiatric disease as the only chronic disease, and pregnant women with diabetes and heart disease (these women already receive specialized care programs at Rigshospitalet).

### Recruitment procedure

As a part of the standard antenatal care contacts, women who fulfill the study criteria will be invited to participate in the study by a midwife from the antenatal clinic responsible for the coordination of specialized antenatal care. Eligible participants who verbally consent to receive more information about the study will be given written information and subsequently contacted by telephone by one of the investigators. If the woman is still interested in receiving information about the study, preliminary questions will be answered. Thereafter, the woman is given the choice between having a face-to-face meeting at the hospital or receiving additional information by telephone. At the face-to-face meeting or during the telephone conversation, more detailed verbal information about the study will be provided by one of the investigators, and the potential study candidate will have the opportunity to ask further questions about the study. If the woman decides to participate, written informed consent will be obtained by the investigator, and the baseline questionnaire will be completed. The randomization and allocation to one of the two RCT arms will be carried out by one of the investigators. The choice between mode of receiving information, either by telephone or face-to-face, is done to accommodate women who do not live near the hospital or have other reasons to prefer receiving information by telephone. A Danish RCT study tested the effect of face-to-face versus telephone information when including study participants and found no differences in level of comprehension between the two groups [31].

### Randomization and blinding

After informed consent is obtained, participants are randomized by one of the investigators to either the ChroPreg intervention plus standard care or standard care alone in a ratio of 1:1. The allocation sequence is computer-generated and nonstratified with varying block sizes concealed to the researchers. The allocation will be centrally conducted using the EasyTrial online clinical trial management and randomization system (easytrial.net, Aalborg, Denmark). After allocation, the participants will be informed about the allocation and further plan of the trial.

The specialized midwives (SM) who will deliver the intervention will not be blinded to the allocation, and neither will the participants. However, the research staff who will collect data from medical records and questionnaires will be blinded to treatment allocation, as will the chief investigator ([name]) and the trial statistician (SR).

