### Intervention

#### Standard care alone

Participants allocated to the control group will receive standard care alone. Pregnant women with chronic disease are considered to have high-risk pregnancies and are referred to the appropriate level of specialized maternity care. All pregnant women with chronic disease will be followed by an obstetrician, and an individual care plan is designed considering the character and severity of the disease and the pregnancy-associated risks. Routinely in Denmark, all pregnant women, including pregnant women with chronic diseases, are also followed by midwives during pregnancy. The standard care appointments for midwife consultation are timed approximately around weeks 14–18, 28, 35, 38, and 40 and include physical examinations, discussion about lifestyle, symptoms of normal and complicated pregnancies, breastfeeding, and preparation for delivery. At Rigshospitalet, two auditorium prenatal classes (90 min each) are delivered by a midwife. The classes provide information about what to expect during birth (contractions, pain relief, possible complications, and interventions) and in the puerperium (breastfeeding and family building). After childbirth, women can contact the department and request a conversation about the delivery with a midwife, and women who have experienced severe or unexpected complications may be offered a postnatal consultation with an obstetrician.

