### Data analysis

Analyses are to be performed on the basis of the intention-to-treat principle. The log-transformed number of days in the hospital in the two groups will be compared in the primary unadjusted analysis, and in a secondary analysis, adjustments will be made for parity and age. Analysis will be performed using the general linear model unless we find a generalized linear model (e.g., Poisson or negative binomial) to fit the distribution of the number of days in the hospital. Furthermore, the two groups will be compared with respect to the proportion of women with 3 or fewer days in the hospital. Comparison of secondary and exploratory outcomes will similarly be performed using the general or generalized linear models as appropriate. In case of an uneven allocation of pregnancies with congenital malformations or chromosomal abnormalities to the two groups, analyses will be performed in the subgroup of women without pregnancies with congenital malformations or chromosomal abnormalities.

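### The adjusted length-of-stay model fixes parity and age as its only covariates, so it cannot account for type of chronic disease: a loss of precision and of an imbalance check in a secondary analysis, not a bias

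*Protocol article*

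**What the plan says.** Under Randomization and blinding, allocation is "standard care alone in a ratio of 1:1", and "The allocation sequence is computer-generated and nonstratified with varying block sizes concealed to the researchers".

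Under Data analysis, three LOS comparisons are planned:
- The main one has no covariates: "The log-transformed number of days in the hospital in the two groups will be compared in the primary unadjusted analysis".
- One adjusted model follows: "in a secondary analysis, adjustments will be made for parity and age".
- The third names no covariates: "the two groups will be compared with respect to the proportion of women with 3 or fewer days in the hospital".

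The only provision for uneven allocation concerns the fetus and leads to a subgroup analysis: "In case of an uneven allocation of pregnancies with congenital malformations or chromosomal abnormalities to the two groups".

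On disease, Inclusion and exclusion criteria admits women with one or more chronic diseases diagnosed before pregnancy. It leaves out diabetes, heart disease and psychiatric disease on its own. Specialized midwives lists about ten disease groups in the training. The Background describes courses that differ from woman to woman: "their chronic disease may be worsened by pregnancy [13], whereas in other cases of disease, women may experience remission from symptoms during pregnancy". Standard care alone says that "an individual care plan is designed considering the character and severity of the disease and the pregnancy-associated risks".

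**The concern.** Disease type is the eligibility criterion, so it is recorded for every woman before randomization at no extra cost. The article itself gives reasons to expect it to matter for days in hospital, since both the course in pregnancy and the care plan depend on it. Even so, allocation does not enforce balance on it, and the one adjusted LOS model has a short, closed covariate list that omits it.

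Two things are at stake in that secondary model. First, any difference in LOS between diseases stays in the residual variance and widens the interval. Second, if the baseline table shows a visible difference in disease mix, the planned adjusted analysis cannot say how much of the estimate is due to it. Adding disease at that stage, after unblinding, would be a data-driven choice.

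**Working it through.** **Inputs from the documents** (Sample size calculation): 25% reduction, that is log(0.75) = −0.2877, printed as −0.29; SD of log LOS 0.80; power 0.80; alpha 0.05; 123 analysed per group. Sidedness is not stated, but two-sided fits and one-sided (95 to 96 per group) does not.

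**The plan's own figure.** The exact two-sample t test at 80% power needs 122.4 per group with 0.2877, which rounds up to the stated 123. (With the rounded 0.29 it needs 120.4.) At 123 per group and 0.2877, power is 80.2%. The sample size reproduces.

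**Inputs by assumption.** The documents give no LOS by disease. Let R² be the share of the variance of log LOS that disease group explains. For simplicity, parity and age are taken to explain nothing.

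**Precision in an adjusted model.** Residual SD = 0.80 × √(1 − R²); SE of the difference = residual SD × √(2/123); sample with the same precision = 123/(1 − R²) per group. The few degrees of freedom used by the covariate are ignored.

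| R² | residual SD | SE | power at 123 per group | equivalent n per group without the covariate |
|---|---|---|---|---|
| 0 | 0.800 | 0.102 | 80.2% | 123 |
| 2% | 0.792 | 0.101 | 81.0% | 126 |
| 5% | 0.780 | 0.099 | 82.2% | 129 |
| 10% | 0.759 | 0.097 | 84.2% | 137 |
| 15% | 0.738 | 0.094 | 86.1% | 145 |

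Only the adjusted model gains. The unadjusted primary test stays at the R² = 0 row, whatever R² is.

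**Chance imbalance.** Take a disease group with prevalence 20% (assumed).
- SE of the difference in prevalence between arms = √(2 × 0.2 × 0.8/123) = 0.051, so 1.96 SE = 0.100, or 10 percentage points.
- If women in that group have log LOS higher by 0.5 (assumed; R² = 0.2 × 0.8 × 0.25/0.64 = 6.25%), the estimate moves by 0.5 × 0.100 = 0.050. With 0.3 instead of 0.5 it moves by 0.030.
- Set against the target of 0.2877, these are 17% and 10%. Set against the standard error of the primary estimate, 0.80 × √(2/123) = 0.102, they are 0.49 and 0.29 of one standard error.

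**Validity of the unadjusted test.** A simulation with 123 per arm, 10,000 runs per setting and a prognostic covariate left out of the model gave rejection rates under no effect of 0.050, 0.048 and 0.054 at R² of 0, 0.10 and 0.20. Type I error is kept.

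**The case against.** The strongest reply is that nothing here is an error. Blocked randomization without strata, followed by an unadjusted primary analysis, is a valid design. Randomization balances disease in expectation, and the unadjusted confidence interval already allows for chance differences in disease mix. That stands.

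Three stronger readings are tempting, and the documents do not support them:
- *The primary estimate is biased.* It is not. A particular allocation may be uneven, but that is sampling variation of about half a standard error in a fairly extreme case, and the error rate is kept.
- *The trial is underpowered because disease mix adds noise.* The SD comes from 426 women with chronic diseases at the same hospital, described without restriction to one disease. Variation between diseases is presumably already in the 0.80 and paid for in the 123 per group. Whether those women included the diabetes and heart disease groups that the trial excludes is not stated.
- *Randomization should have been stratified by disease.* About ten groups among 258 women would give sparse strata, and Trial status reports 130 women already included by May 2019.

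It can also be said that no section states that LOS differs between the eligible diseases. The Background speaks of disease course, Standard care alone of care planning, and the list of ten groups is a training syllabus rather than an enrolled case mix. This is fair, and it is why the size can only be given as a range; at R² of 2% the gain is under one power point.

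Finally, an analysis plan that is not shown may add covariates. But the article does not leave the covariates open. It names them, so the point concerns a stated choice and not a missing detail.

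**Conclusion.** The point holds in a limited form. The article commits the secondary adjusted LOS analysis to parity and age, and so leaves out a baseline factor that is known for every woman and that the article itself links to course and care. The consequence is lost precision and no planned check of imbalance in disease mix, both confined to that secondary model. The primary analysis and the sample size stand.

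The size rests on the assumed R², disease prevalence and disease effect, and on the linear model for log LOS. The article allows a Poisson or negative binomial model instead, for which the figures would differ. Under these assumptions the effect is small to moderate. The change is worth making because it costs little and must be made before unblinding to be credible.

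**What to change.** In Data analysis, add baseline chronic-disease group to parity and age in the adjusted LOS model. Use a small number of levels, for example 4 to 6 with rare diagnoses pooled, assigned from the diagnosis recorded at inclusion.

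Fix two things in writing before unblinding:
- the grouping itself; the 2017 data on 426 women could help to form it if they are coded by diagnosis, which the article does not say;
- a rule for women with more than one disease, for example the main diagnosis for which the obstetrician follows her, or a separate level for several diseases.

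Randomization and the unadjusted primary analysis stay as they are. The cost is a line of analysis text, coding of a diagnosis already needed for eligibility, and 3 to 5 degrees of freedom with 246 women analysed. Pooling is somewhat arbitrary, and a coarse diagnosis group does not capture severity. No patients or visits are added.
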